**Daily**
1 tablespoon of olive oil.≥2 portions of fruit.≥3 portions of vegetables.≥2 portions of wholegrain foods (including wholemeal bread, wholegrain rice, whole wheat pasta).≥2 portions of dairy foods (including, milk, cheese, yoghurts) or plant protein alternatives.Moderate alcohol (1-2 glasses of wine/beer consumed with meals) for alcohol consumers.
**Weekly**
Preferential consumption of chicken and oily fish over red meat, ≥2 portions of each and red meat <2 portions.3 handfuls of natural nuts (90 g).

Written materials (PROMED diet guide and recipe book) will be provided to support adoption of diet behaviours. Participants will be given a recipe book with suggested quick, low-cost menu plans and practical dietary tips to overcome small appetite. Key foods will be delivered to their home free of charge for the first 3 months to encourage adoption of the PROMED diet behaviours. Foods will be self-selected by participants from a predefined list to facilitate personal preference and will include olive oil, fruits and vegetables, wholegrain foods (cereals, breads, rice and pasta), nuts, nut butters, canned oily fish and low-fat dairy foods.

##### Exercise intervention

The exercise intervention has been adapted from a commercially available ‘ExWell@home’ group exercise rehabilitation programme that is acceptable to older adults and suggested to improve health outcomes in those with chronic disease.^54^ The home-based exercise intervention comprises strength, aerobic, core stability and balance exercises available across four levels of ability: (1) chair based, (2) basic, (3) standard and (4) advanced. After the dietary education session, participants will receive a personal exercise prescription involving a written plan, demonstration of exercises suitable for their fitness level and instruction on safety aspects to minimise injury risk. A researcher trained to deliver the adapted ExWell Programme will determine baseline fitness level using measured blood pressure, pulse rate, short physical performance test results, handgrip strength test obtained from the baseline study visit and their assessed performance in a ‘basic level’ class.

Participants will be asked to report their perceived intensity of exertion using the Borg Rate of Perceived Exertion Scale^6–20 55^ aiming for ‘somewhat hard’ within a range of 12–14 points. Participants will be instructed to increase or decrease the frequency and intensity of exercise over the first 4 weeks to meet the intervention target of two 30–60 min moderate-intensity exercise sessions per week. Participants will receive additional supportive materials to achieve their exercise goals including pre-recorded exercise classes, a written home-based exercise resource, a pedometer and exercise diary.

#### Group 2: PROMED

Participants will receive only the protein-enriched MedDiet intervention and will be advised to keep other lifestyle factors unchanged throughout the study period, including maintenance of their usual physical activity level.

#### Group 3: standard care

Participants will receive a general healthy eating diet sheet provided at baseline. To encourage retention in the study, personalised dietary advice and written materials will be offered to control group participants upon completion of the final study assessment.

##### Maximising and monitoring compliance with the diet and exercise interventions

For study participants randomised to the PROMED-EX and PROMED interventions (groups 1 and 2, respectively), several approaches will be used to facilitate behaviour change and encourage compliance with the diet and exercise goals. The initial education session will be scheduled at a convenient time for the participant and in a convenient location (either in a dedicated research facility, the participant’s own home or via remote video call). Partners or caregivers who are responsible for food preparation and/or shopping will also be invited to the education session if applicable. Furthermore, techniques demonstrated to support diet and exercise behaviour change have been incorporated into the intervention written materials and include ‘instruction on how to perform behaviour’, ‘action planning’, ‘self-monitoring’ and ‘problem-solving’.^56^

Participants will be encouraged to self-monitor their compliance in achieving the diet and exercise goals where applicable. The researcher will contact participants weekly via telephone during the first 3 months to review individual progress, monitor compliance and body weight, deal with any difficulties participants may be experiencing in meeting their goals and provide support and personalised feedback as required. Participants will also be able to contact the researcher at any time during the 6-month intervention period.

### Data collection and study outcomes

Participants will meet with a researcher at baseline and after 3 and 6 months to complete a study assessment lasting no longer than 2.5 hours. The assessment will take place in a dedicated research facility at Queen’s University Belfast (QUB) or in the participant’s home if preferred. A summary of the outcomes and data collection measures at study time points is found in table 2.

**Table 2 T2:** Overview of study data collection variables and measures

Study outcomes	Data collection variables/measures	Baseline	3 months	6 months
Primary outcome				
Nutritional status (6 months)	Mini Nutrition Assessment (MNA) Long-Form Questionnaire^57^	✓		✓
Secondary outcomes				
Nutrition and body composition				
Nutritional status (midpoint change)	MNA Long-Form	✓	✓	
Nutritional intake	PROMED diet score questionnaire and 4-day food diary	✓	✓	✓
Appetite	Simplified Nutrition Appetite Questionnaire^60^	✓	✓	✓
Body composition	Bioelectric impedance analysis of body water, fat and lean muscle mass (BodyStat 1500 MDD)	✓	✓	✓
Anthropometry	Height (stadiometer) and weight (digital scales); waist circumference	✓	✓	✓
Physical activity				
Physical activity	Recent Physical Activity Questionnaire^62^	✓	✓	✓
Cognitive function				
Cognitive function	Catch-Cog,^63^ Trail Making Test A and B,^64^ and Delayed Recall Test	✓	✓	✓
Physical strength and function				
Functional capacity	Short Physical Performance Battery^65^	✓	✓	✓
Muscle strength	Hand Grip Strength hydraulic dynamometer (Baseline)	✓	✓	✓
Psychosocial				
Health-related quality of life	SF-36 Health Survey^66^ Questionnaire	✓	✓	✓
Depressive symptoms	Geriatric Depression Scale^67^ Questionnaire	✓	✓	✓
Blood pressure				
Blood pressure	Clinic-measured blood pressure (Omron Healthcare)	✓	✓	✓
Biochemical measures				
Blood biomarkers	Nutritional: vitamins A and E, and carotenoids Cardiometabolic: lipid profile, HbA1c, glucose and insulin Inflammatory: hs-CRP, IL-6 Metabolomic analysis	✓	✓	✓
Evaluation				
Study evaluation	Questionnaire			✓

hs-CRP, high-sensitivity C reactive protein; IL, interleukin.

### Primary outcome

The primary study outcome is between-group difference in change in nutritional status at 6 months using the validated MNA score (MNA 0–30).^57^ The MNA is the most widely validated tool for detecting undernutrition risk in older adults^58^ and is shown to respond to dietary intervention.^47^

### Secondary outcomes

#### Nutrition and body composition

Change in MNA score will be analysed at midpoint (3 months from baseline). Dietary behaviour will be reported using the PROMED diet score (range 0–14) adapted from a validated Spanish Mediterranean diet score^59^ to incorporate the higher protein food targets and tailored for a Northern European population. Higher scores indicate increased concordance with the PROMED diet. Overall dietary intake will be assessed using a 4-day prospective food diary. Participants will be instructed to record all items of food and beverages consumed over 4 consecutive days (2 weekend days) at home and provide details of the portion size consumed, cooking methods and named brands. Data on self-reported appetite will also be collected using the four-item Simplified Nutrition Appetite Questionnaire (SNAQ) validated for older community-dwelling adults.^60^ Lower SNAQ scores indicate poorer appetite. Body composition will be assessed using non-invasive bioelectrical impedance analysis (BodyStat 1500 MDD) to estimate body water, fat and lean muscle mass.^61^ Anthropometric measures of weight, height and waist circumference will also be taken using digital scales, a stadiometer and flexible measuring tape, respectively.

#### Physical activity

Time spent on different intensity levels of physical activity will be self-reported using a validated Recent Physical Activity Questionnaire across four domains: home, commuting, occupational activity (if appropriate) and leisure activity over the previous 4 weeks.^62^

#### Cognitive function

A brief neuropsychological test battery (NTB) will be administered by a trained researcher to capture cognitive domains that are shown to be sensitive to progression in early stages of memory decline: global cognition, executive functioning, episodic and working memory, information processing speed and sustained attention.^63^ The NTB will include the Catch-Cog assessment^63^ comprising (1) three Alzheimer’s Disease Assessment Scale–Cognitive subscales (Word Recognition (score range 0–12), Word Recall (score range 0–10) and Orientation (score range 0–8)) to assess episodic memory; (2) the Controlled Oral Word Association Test (number of acceptable words in 1 min) and Category Fluency Test (number of animals named in 1 min); (3) Digit Symbol Substitution Test (total number of correct symbols in 90 s); and (4) Digit Span Backward (score range 0–14) to assess executive function and working memory. The Trail Making Test (A and B) will be used to assess information processing speed and attention.^64^ A delayed recall test of recalled learnt words after a 5-minute delay (score range 0–10) will be administered, with higher scores indicating better memory performance. Summary composite scores will be created for global cognition and domains of memory and executive function.

#### Physical strength and function

Lower extremity functional status will be measured using the Short Physical Performance Battery (SPPB).^65^ The SPPB includes three timed tasks to assess walking speed, chair stand and standing balance, with scores ranging from 0 (worst performance) to 12 (best performance). Muscle (handgrip) strength will be measured with a calibrated dynamometer (Baseline) (kg) using a standard procedure.^48^

#### Psychosocial

Health-related quality of life (HRQoL) will be determined by using the Short-Form 36-item Questionnaire (SF-36),^66^ which measures eight domains of health status: physical functioning, role limitations due to physical issues, role limitation due to emotional problems, energy/fatigue, emotional well-being, social functioning, pain and general health perception. SF-36 scores range from 0 to 100 with higher scores indicating better HRQoL.^66^ Depressive symptoms will be determined using the 15-item Geriatric Depression Scale (GDS)–Short-Form. GDS scores range from 0 to 15, with a score ≥5 suggesting depression.^67^

#### Blood pressure

Systolic and diastolic blood pressure (mm Hg) will be measured three times in the dominant arm after a 5-minute rest in the seated position using a calibrated automated device approved by the British Hypertension Society (Omron Healthcare). The first measure will be discarded and the average of the final two measurements will be recorded.

#### Biochemical measures

A 50 mL fasting peripheral venous blood sample will be taken at the start of each study assessment for metabolomic profiling and biomarker measurement. Anonymised samples will be processed in the nutrition laboratory at QUB according to standardised protocols and stored in aliquots at −80°C until analysis. Biochemical markers relating to nutrition (vitamins A, E and carotenoids), metabolic (lipid profile, HbA1c, glucose and insulin) and inflammation (high-sensitivity C reactive protein, interleukin-6) will be measured. Plasma samples will be transferred to University College Dublin for metabolomic analysis.

#### Evaluation

A questionnaire will be administered at the end of the study to determine acceptability and tolerance of the intervention and the overall experience of taking part in the study. Participants will be asked to return diet and exercise logs to evaluate engagement with the intervention.

### Data management and statistical analysis plan

Data will be de-identified and stored securely according to General Data Protection Regulation and UK Data Protection Act 2018 in QUB. There are no plans for interim study analysis. The groups will be similar due to randomisation; therefore, there are no a priori plans to include covariates in the analyses. Participant characteristics by allocated group will be compared using ANOVA for continuous variables and χ^2^ test for dichotomous variables. Skewed variables will be log-transformed prior to analysis. An intention-to-treat analysis will be conducted using multiple linear regression model to compare MNA score at 6 months between the three groups adjusting for baseline. Dunnett’s procedure will then be used to compare each intervention group to the controls, accounting for multiple testing. Analysis of secondary outcomes will use a similar method and these exploratory analyses will be interpreted cautiously. Sensitivity analyses will be conducted to evaluate the diet and exercise behavioural changes maintained over 6 months and to determine the effect of intervention compliance on study endpoints. Multiple imputations for missing data will be used if required. Analyses will be performed using STATA Statistical Software (StataCorp).

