### Sample size

As no prior studies have evaluated the effects of whole diet and exercise on nutritional status and cognition, the sample size calculation is based on an SD of the change in Mini Nutritional Assessment (MNA) score of 4 points over a similar period from the control group of a previous nutrition intervention.^47^ A total of 28 completing in each intervention and control group would provide over 80% power to detect a difference in the three means, based on a statistically significant analysis of variance (ANOVA) result at the 5% level, hypothesising a true increase in MNA of 3 or more in both intervention groups, but not the control group. Loss to follow-up is estimated from our prior experience of conducting lifestyle trials in older adults^48–50^ where attrition ranges from 6%^50^ to 30%.^49^ Considering, FINGER^42^ evaluated an intensive multidomain lifestyle intervention among older adults at increased dementia risk and reported 12% withdrawal over 2 years. We anticipate dropout at 20% and therefore have added 20% to the sample size to account for non-compliance, dropout or discontinuation.

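### Step-down Dunnett for the two comparisons with control would raise power to show that both interventions work from about 57% to 67%, with no extra participants and familywise error still within 5%

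*Protocol article*

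**What the plan says.** The Sample size section of the protocol article takes an "SD of the change in Mini Nutritional Assessment (MNA) score of 4 points" and states that "A total of 28 completing in each intervention and control group would provide over 80% power". That power is "based on a statistically significant analysis of variance (ANOVA) result at the 5% level". The effect assumed for this calculation is given as "hypothesising a true increase in MNA of 3 or more in both intervention groups, but not the control group". The allowance for 20% dropout brings the trial to 35 per arm, 105 in all.

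The Data management and statistical analysis plan section uses multiple linear regression, by intention to treat, to "compare MNA score at 6 months between the three groups adjusting for baseline". The comparisons with standard care form the next step, for which Dunnett's "procedure will then be used to compare each intervention group to the controls, accounting for multiple testing". The article does not name the form of Dunnett's procedure, and it does not say what role, if any, an overall three-group test plays in the primary conclusion.

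**The concern.** The introduction frames the aim as the effect of each intervention, diet with and without exercise, compared with standard care. The two comparisons with control answer that aim, and the Sample size section assumes that both interventions work. The chance of showing both is therefore a natural measure of the procedure.

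Single-step Dunnett holds both comparisons to the same raised critical value. Once the larger contrast has passed that value, the hypothesis that neither intervention works has been rejected. Closed testing then allows the other contrast to be tested at the ordinary 5% t value. Step-down Dunnett does this. It rejects everything that single-step rejects and sometimes more, under the same 5% familywise bound. At stake is avoidable loss of power for the second intervention.

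**Working it through.** **Inputs.** From Sample size: SD of change 4, 28 completers per arm, mean changes +3, +3 and 0, 5% level. Assumptions: two-sided tests, pooled variance, equal arms (so the two contrasts have correlation 0.5), single-step as the default form of Dunnett, and at first no gain from baseline adjustment.

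**The plan's own figure.**
- The grand mean is 2, so the sum of squared deviations is 1 + 1 + 4 = 6.
- Noncentrality is 28 × 6 / 16 = 10.5, on 2 and 84 − 3 = 81 degrees of freedom.
- Power of the F test is 82.0%, which agrees with the stated figure of over 80%.
- 28 / 0.8 = 35 per arm and 3 × 35 = 105, as stated.

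**Critical values on 81 df.** The two-sided Dunnett value for two contrasts is 2.251. The ordinary t value is 1.990. The standard error of a difference is 4 × √(2/28) = 1.069. At SD 4, single-step therefore needs an observed difference of 2.251 × 1.069 = 2.41 MNA points for each comparison. Step-down needs 2.41 for the larger and 1.990 × 1.069 = 2.13 for the other.

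**Decision rules.** Single-step shows both if the smaller |t| exceeds 2.251. Step-down shows both if the larger |t| exceeds 2.251 and the smaller exceeds 1.990.

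**Power, 2 million simulated trials with gains 3/3/0.**

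| | Single-step | Step-down |
|---|---|---|
| Both interventions | 57.2% | 66.9% |
| A given intervention | 71.0% | 75.9% |
| At least one | 84.9% | 84.9% |

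The rows are consistent, because power for at least one equals twice the power for a given intervention minus the power for both. Single-step: 2 × 71.0 − 57.2 = 84.8. Step-down: 2 × 75.9 − 66.9 = 84.9. Both agree with the table within rounding.

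**Familywise error.** With all three groups equal, it is 5.0% for both forms. With one arm very strongly effective and the other ineffective, error on the ineffective arm is 2.7% single-step and 5.0% step-down. The 5% bound holds for both, but step-down uses all of it in that case.

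**Effect of an overall F test as a gate.** With an F gate in front of single-step Dunnett, power for both stays at 57.2% and power for at least one falls from 84.9% to 81.7%. The gain for both interventions therefore comes only from stepping down. Leaving out a gate protects about 3 points of power for at least one.

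**Sensitivity to the planned baseline adjustment.** The article gives no correlation between baseline and change, so r is assumed. The residual SD is 4 × √(1 − r²), with one degree of freedom fewer.
- r = 0.3: SD 3.82; power for both goes from 62.7% to 71.9%, a gain of 9.2 points.
- r = 0.5: SD 3.46; power for both goes from 74.0% to 81.6%, a gain of 7.6 points.

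With no dropout (35 per arm) and no adjustment gain, it goes from 70.7% to 78.9%.

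**The case against.** A reader might infer that the primary outcome is tested twice, with no deciding test and an uncertain error rate. The document does not support this. The Sample size section uses the ANOVA as a basis for sizing and sets no rule for success. The analysis section names no F-test threshold and no gate. The natural reading is one fitted model followed by two contrasts, with the multiplicity adjustment attached to Dunnett alone. That is valid at 5%. A familywise error of 3.7% (F gate before Dunnett) or 6.3% (a significant F or a significant Dunnett result counts as success) can be calculated, but each needs a rule that the article does not state.

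A reader might also infer that the trial is underpowered because 57% is below 80%. The article sets its power target for a difference among three means, not for winning both comparisons, and that target is met. The 57% also ignores the planned baseline adjustment.

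Two further objections stand in part. First, single-step is the usual reading of the procedure's name but is not written; if step-down was intended, only the wording needs to change. Second, single-step Dunnett is a legitimate choice whose simultaneous intervals agree with its p-values. Step-down loses that agreement and spends more of the error allowance when only one arm works. These are real costs to weigh against a gain of 8 to 10 points.

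**Conclusion.** The point holds as an inexpensive improvement, not as an error. On the document's own inputs without adjustment gain, step-down Dunnett adds about 10 points of power to show that both interventions work (57% to 67%) and about 5 points for a given comparison (71% to 76%). It adds nothing for at least one (85%). Under assumed baseline-change correlations of 0.3 to 0.5, both levels are higher and about 8 to 9 points of the gain for both remain. These sizes rest on 28 completers in each arm, SD 4, equal true gains of 3 in both interventions, and a single-step reading of the current text.

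**What to change.** In the Data management and statistical analysis plan section:

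- Make the two baseline-adjusted comparisons with control, tested by step-down Dunnett (two-sided, familywise 5%), the deciding primary test: the larger contrast against the Dunnett critical value and, if significant, the other against the ordinary 5% t value.
- State that both comparisons are carried out whatever the overall three-group result, which is descriptive.
- Report single-step Dunnett 95% confidence intervals for estimation beside the step-down p-values.

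The cost is a few sentences and no participants, and the change should be fixed before the data are analysed. The downside is that a single-step interval may occasionally include zero when the step-down p-value is below 5%; the text should say so in advance.

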### Ethics and dissemination

Ethical approval has been received from the Office for Research Ethics Committee (OREC) (ref: 21/NW/0215) and the trial has been registered on ClinicalTrials.gov (NCT05166564). The study will be reported according to Consolidated Standards of Reporting Trials guidelines for parallel-group randomised trials.^68^ Written informed consent will be obtained from all study participants prior to study enrolment and any adverse events will be reported to the study sponsor (QUB) and OREC.

Study findings will be of interest to a range of stakeholders in the areas of healthy ageing, preventable malnutrition, cognitive decline and dementia risk reduction, including academics, the public, healthcare professionals and clinicians, charitable organisations and industry. Findings will be published in academic journals and published in open-access repositories, for example, the JPI-HDHL Meta Database (https://www.healthydietforhealthylife.eu/) knowledge transfer platform.

## COVID-19

The research team will comply with public health and QUB guidance regarding COVID-19. Several strategies will be implemented to mitigate risk: (1) COVID-19 risk screening for participants prior to study visits, (2) optional home study visits, (3) optional remote delivery of intervention support, (4) personal protective equipment for researchers conducting study assessments, (5) participant face coverings for study visits, (6) social distancing measures followed where possible and (7) researcher lateral flow testing prestudy visit.

